#### Pain

A range of pain scales are utilized to measure pain intensity (assessed by child, nurse, or parent). The Faces Pain Scale-Revised (FPS-R) [49] is used to assess the child’s self-report of pain and will be the primary outcome measure. Convergent validity of the FPS-R is supported by a strong positive correlation (*r* = 0.93, *p* < 0.001, *N* = 76) with a visual analog scale (VAS) pain intensity measure in children aged 5–12 years and by strong positive correlations with the VAS (*r* = 0.92, *p* < 0.001, *N* = 45) and the color analog scale (*r* = 0.84, *p* < 0.001, *N* = 45) in a clinical sample of pediatric inpatients aged 4–12 years [49]. Even among the youngest patients sampled (four-year-olds), there is evidence of usage of the FPS-R and analog scales in a consistent and reliable manner [49]. Nurses report a behavioral/observational rating on the Face, Legs, Arms, Cry, Consolability (FLACC) scale [50, 51]. The FLACC scale has been validated for use in settings such as postoperative pain [50]. Despite a recent systematic review rescinding recommendation of the FLACC scale for procedural pain assessment [51], we have chosen this scale in the absence of an acceptable alternative due to its extensive use in prior clinical trials examining procedural pain. Parents also rate their child’s pain using an 11-point (0 to 10) numeric rating scale (NRS) [52]. Pain scores reported verbally by the parent (NRS) and child (FPS-R) are documented by the primary investigator. Nurses document the FLACC pain scores.

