#### Wound healing

Re-epithelialization is defined as ≥95 % wound healing and no further wound dressings required. Scabs or crusts are defined as unhealed areas [53]. For the purpose of the main analysis, this outcome measure will be assessed using the percentage re-epithelialization assessed from 3D digital photography by an independent surgeon and nurse blinded to study treatment group. The percentage re-epithelialization reported by the independent surgeon will be used in the main analysis if appropriate. The outcome will also be measured from 3D digital photography by the investigator ([name]), and the time to wound healing recorded in the medical records will also be used for comparative purposes. Wound photographs are taken at each dressing change using 3D LifeViz System™ (Quantificare, Sophia Antipolis, France) [54]. The independent blinded surgeon and nurse will mark out the wound edges after the photographs are taken, along with any unhealed areas. Surface area computer mapping will then be used to determine percentage re-epithelialization [53, 54].

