Analyses will be conducted with data stratified for burn depth (superficial partial-thickness/deep partial-thickness/full-thickness) and participant age (e.g., <8 years/≥8 years, with age strata based on age-group validity of the VAS-A) [69]. Differences in hypnotic responsivity between the intervention group and a normative comparison group will be analyzed using z-scores or using equivalent non-parametric tests such as the Mann-Whitney *U* test where applicable. Differences in re-epithelialization by the independent blinded raters (surgeon and nurse) and the investigator ([name]) will be examined using reliability coefficients and measures of agreement (e.g., percentages of exact agreement). Differences between measures of pain (e.g., observer report by parents versus child self-report) will be examined using correlational analyses where appropriate.

The influence of demographic and clinical factors, and primary and secondary outcomes not included as dependent variables, on primary and secondary outcomes will be examined using regression models and GEE models. Post hoc adjustment for multiple comparisons will be conducted using the Šidák correction [70] where appropriate. Statistical significance will be set at *p* < 0.05.

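### The only method named for examining differences between pain raters is correlation, which cannot show a systematic difference

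*Protocol article*

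**What the plan says.** Three people rate the child's pain, each on a different instrument (Outcomes, Pain). The child uses the FPS-R, which "is used to assess the child’s self-report of pain and will be the primary outcome measure". For the parent, "Parents also rate their child’s pain using an 11-point (0 to 10) numeric rating scale (NRS"). The nurse scores the FLACC.

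Data analysis then sets out how these ratings will be compared: "Differences between measures of pain (e.g., observer report by parents versus child self-report) will be examined using correlational analyses where appropriate". No other method is named for comparing the pain measures with one another.

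The Sample size section gives a minimum clinically important difference of 2 points, with an SD of 2.5, for the pain outcome measures in the plural.

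**The concern.** The question and the method do not match. Asking whether parent and child ratings differ means asking whether one is systematically higher, by how much, and how far apart individual pairs lie. Correlation asks only whether the two rise and fall together. It is unaffected by a constant shift and by a proportional one.

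The practical stake is interpretation. Hypnosis cannot be masked (Blinding), and self-report, parent report and nurse report may not tell the same story about pain. A reader would then want to know whether parents habitually under-rate or over-rate relative to their children. A high correlation could be taken as reassurance while leaving that unexamined.

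Because the article states both the question and the method, this is not a detail left to a fuller document.

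**Working it through.** The plan states no figure for agreement between pain raters, so there is none to reproduce. The check is whether correlation responds to a systematic gap.

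**Inputs**
- Child score SD 2.5 and pain MCID 2: Sample size section.
- Parent rating = child rating + shift *b* + independent noise with SD *s*. The protocol gives no *s*. I assume 1.5 and show 1.0 and 2.0 as a range.
- Both scores on one 0-10 metric: an assumption. The article gives the NRS range but not the FPS-R scoring range.
- Floor and ceiling effects are ignored in the formulas.

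**Formulas**
- Child variance = 2.5² = 6.25. Parent variance = 6.25 + *s*². Covariance = 6.25.
- Pearson r = 6.25 / (2.5 × √(6.25 + *s*²)). The shift *b* does not appear.
- Concordance coefficient = 2 × 6.25 / (6.25 + 6.25 + *s*² + *b*²). Here *b* does appear.
- Limits of agreement = *b* ± 1.96 × *s*.

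**Main case, s = 1.5**

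r = 6.25 / (2.5 × √8.5) = 6.25 / 7.289 = 0.86. Concordance = 12.5 / (14.75 + *b*²). Limits = *b* ± 2.94.

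| Parent minus child, *b* | Pearson r | Concordance | Limits of agreement |
|---|---|---|---|
| 0 | 0.86 | 12.5 / 14.75 = 0.85 | −2.94 to 2.94 |
| −1 | 0.86 | 12.5 / 15.75 = 0.79 | −3.94 to 1.94 |
| −2 (the MCID) | 0.86 | 12.5 / 18.75 = 0.67 | −4.94 to 0.94 |
| −3 | 0.86 | 12.5 / 23.75 = 0.53 | −5.94 to −0.06 |

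A simulation of 200,000 pairs per shift, on the same inputs with parents scoring higher rather than lower (the sign does not matter, since *b* is squared), gave r of 0.857 to 0.859 and concordance of 0.848, 0.794, 0.666 and 0.526.

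**Range over the assumed noise**
- *s* = 1.0: r = 2.5 / √7.25 = 0.93 at every shift. Concordance falls from 12.5 / 13.5 = 0.93 with no shift to 12.5 / 17.5 = 0.71 at 2 points.
- *s* = 2.0: r = 2.5 / √10.25 = 0.78 at every shift. Concordance falls from 12.5 / 16.5 = 0.76 to 12.5 / 20.5 = 0.61.

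The noise sets the level of r. The shift never moves it.

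**The case against.** **Different instruments.** FPS-R, NRS and FLACC are not one scale used by three raters. Correlation is a standard way to show convergence across scales, and the Pain section cites correlations for the FPS-R in exactly that way. Limits of agreement need a common metric, which the article does not establish. This stands as a limit on the remedy, but it does not rescue the sentence. The aim is worded as differences, not convergence, and the Sample size section applies one point difference to the pain measures together.

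**Descriptive summaries.** Data analysis also promises means, SDs and confidence intervals for outcome measures, so a 2-point gap between average parent and child scores could be noticed. That is fair. But separate summaries give neither the paired difference with its confidence interval nor the spread of individual disagreement. These could be reconstructed from means, SDs and r only if all came from the same pairs at one time point, whereas ratings here repeat at every dressing change.

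**Bounded scales.** An exact constant shift is impossible at the floor: no parent can score 2 below a child who reports 0. Truncation would alter r somewhat, but that would not make r a measure of the shift.

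**A stronger reading.** A reader might infer that the healing-rater analysis has the same fault, because exact agreement is named and percentage re-epithelialization comes from surface-area mapping. The document does not support that. Differences between healing raters "will be examined using reliability coefficients and measures of agreement (e.g., percentages of exact agreement"), so reliability coefficients are planned and exact agreement is only an example. Healing also has a yes/no form, since "Re-epithelialization is defined as ≥95 % wound healing and no further wound dressings required", and percent agreement suits that. Nor does the protocol say that rater agreement decides whether the surgeon's reading is appropriate for the main analysis.

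**Conclusion.** The point holds for the comparison of pain measures only. The protocol asks about differences and names a method that cannot detect a systematic one. A parent-child gap equal to the 2-point MCID leaves r unchanged, at 0.86 in the main illustration and between 0.78 and 0.93 over the assumed noise range. That r ignores a constant shift is algebra and needs no assumption. The particular values rest on the assumed noise SD, a common 0-10 metric and no floor or ceiling effects.

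The consequence is limited. Child self-report is fixed as the primary pain measure and parent ratings do not replace it, so the primary treatment comparison, the sample size and the main conclusions are untouched. A reader might infer that the pain result itself is at risk, but nothing in the protocol supports that. This is a cheap improvement to an ancillary measurement analysis.

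**What to change.** Revise the sentence in Data analysis along these lines:

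- Where two pain scores are on a common 0-10 metric, report the mean paired difference (parent minus child) with a 95% CI and limits of agreement. Allow for repeated ratings per child, for example with a mixed model for the paired differences with a random effect for child.
- Keep the correlation coefficient as a supplementary measure of association.
- Where the scales are not comparable, reword the aim as association between measures and keep correlation as the method.
- State the scoring range used for each pain scale, so that it is clear which pairs qualify.

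The cost is a little more analysis on data already collected. No new measurements or participants are needed, and the primary analysis does not change.

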**Discussion:**

Study results will elucidate whether the disease process can be changed by using medical hypnosis with children to decrease pain, anxiety, and stress in the context of acute burn wounds.

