#### Primary outcome measures

The two primary outcome measures are pain intensity and wound healing (i.e., re-epithelialization time). Pain measurements are taken several times for each participant. The first time point (baseline) is immediately before premedication prior to removal of the wound dressing in clinic. The second time point is immediately after the new dressing is in place; the worst pain is assessed reflecting the maximal pain intensity experienced by the participant during the procedure (retrospective). For the third time point, a final pain assessment occurs to gauge pain intensity immediately after the new dressings are in place and hypnotherapy has ceased. No pain measurements are taken during hypnosis. Assessing pain intensity in this manner effectively gives three time points relative to the procedure: before, during, and after. These measurements take place at each subsequent dressing change until ≥95 % wound re-epithelialization.

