#### PTSD

PTSD severity three months following injury will be assessed using the Child PTSD Symptom Scale (CPSS) [57] for children aged 7 years or older. The CPSS is designed to assess PTSD diagnosis and symptom severity in children ages 8 to 18 who have experienced a single-incident traumatic event [57]. Total symptom score and the three symptom clusters of the CPSS demonstrate high internal consistency (α = 0.89 for total score) [57]. The percentage agreement between PTSD diagnoses at two separate time points was 84 %, indicative of moderately high reliability [57]. Test-retest reliability of the total CPSS score is acceptable (κ = 0.84) [57]. Convergent validity of the CPSS has been supported (Pearson’s *r* = 0.80, *p* < 0.001) when measured against the Child PTSD Reaction Index (CPTSD-RI) [57].

The Young Child PTSD Checklist (YCPC) [58] will be used for children younger than seven years old. Face validity of the YCPC items is excellent based on a series of studies by Scheeringa et al. that used these items in an interview format and formed the basis for the new DSM-5 disorder titled “Posttraumatic stress disorder for children six years and younger” [59–62]. The test-retest reliability (intraclass correlation coefficient = 0.87) [63] was acceptable, and the predictive validity [64] of PTSD symptoms using an interview format has been supported.

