### Sample size

A sample size estimate was derived from the primary outcomes: days to re-epithelialization and pain. Based on re-epithelialization within 15 (SD = 4) days and a minimum clinically important difference (MCID) of 3 days [26], the sample size required was estimated as 29 per group, using 80 % power and an α of 0.05. Allowing for 10 % loss to follow-up, a total of 66 participants will be required. Additionally, this sample size is adequate to show an MCID of 2 (SD 2.5) in the pain outcome measures [26]. Recruitment will continue until at least 33 participants in each arm have been obtained with complete data for the primary outcomes.

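### The plan to examine the influence of outcomes on one another sets no time order and does not name treatment group, so associations could be reported as influences

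*Protocol article*

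**What the plan says.** After the group comparisons, the Data analysis section of the protocol article adds a supplementary analysis, by regression and GEE, whose subject is "The influence of demographic and clinical factors, and primary and secondary outcomes not included as dependent variables, on primary and secondary outcomes". The rule is symmetric: an outcome is a candidate predictor whenever it is not the dependent variable. The number of predictors and the way they enter a model are not stated. The next sentence adds "Post hoc adjustment for multiple comparisons will be conducted using the Šidák correction", qualified as applying where appropriate.

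The outcomes are measured at different times. On pain, the Primary outcome measures section says "These measurements take place at each subsequent dressing change until ≥95 % wound re-epithelialization". Days to re-epithelialization is therefore known only when that series ends. On PTSD, the article says "PTSD severity three months following injury will be assessed".

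Earlier in Data analysis, the main GEE is described with treatment group and time as terms. The same paragraph lists days to re-epithelialization among the potential confounders of pain. On size, the Sample size section says "a total of 66 participants will be required".

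**The concern.** Two features of the sentence cause the difficulty.

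**No time order.** A value obtained three months after injury, or at the end of healing, cannot have influenced pain at a dressing change that came before it. Where pain is tested on final healing time and final healing time on pain, both directions cannot be read as influence from the same data. The reading is not strained, because the confounder list for pain already treats days to re-epithelialization as something that acts on pain.

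**Treatment group not named.** Hypnosis is hypothesized to reduce pain and anxiety and to shorten healing. Two outcomes moved by the same treatment are correlated across the pooled sample even when neither acts on the other.

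At stake is how the links between outcomes are interpreted. The Significance of the study section attaches importance to connections between pain, anxiety, stress and healing time. A significant coefficient could be presented as such a connection when it reflects only the shared effect of treatment or shared burn severity.

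**Working it through.** **Inputs.** From Sample size: healing difference 3 days, SD 4; pain difference 2, SD 2.5; power 80%, α 0.05; 29 per group, 66 in total after 10% loss. Two-sided testing is assumed, since sidedness is not stated.

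**1. The plan's own figure.** n per group = 2(1.960 + 0.842)² × (SD/difference)².
- Healing: 2 × 7.849 × (4/3)² = 27.9, so 28 by the normal approximation. The t-test solution is 28.9, so 29, as stated.
- Loss to follow-up: 29/0.9 = 32.2, so 33 per group and 66 in total, as stated.
- Pain: 2 × 7.849 × (2.5/2)² = 24.5, so 25 per group, and 29 is enough.

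The sample size reproduces. The article gives no figure for the models discussed here.

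**2. Timing.**

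| Quantity | When known |
|---|---|
| Pain, procedural anxiety | around each dressing change |
| Days to re-epithelialization | at the end of the dressing changes |
| PTSD severity | three months after injury |

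Under the symmetric rule, either of the last two may be a predictor of the first. Nothing in the sentence prevents it.

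**3. Effect of leaving group out, planned effects only.** Take one pain value and one healing time per child, 33 children per arm, within-arm SD 1, and no link within arms.
- Standardized effects: pain 2/2.5 = 0.8; healing 3/4 = 0.75.
- Variance of a 0/1 group indicator with equal arms: 0.25.
- Induced covariance: 0.25 × 0.8 × 0.75 = 0.15.
- Pooled variances: 1 + 0.25 × 0.8² = 1.16 and 1 + 0.25 × 0.75² = 1.141.
- Induced correlation: 0.15/√(1.16 × 1.141) = 0.130.
- Fisher z: atanh(0.130) × √(66 − 3) = 0.131 × 7.94 = 1.04.
- Chance of p < 0.05: Φ(1.04 − 1.96) + Φ(−1.04 − 1.96) = 0.179 + 0.001 = 0.18.

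A simulation of 20,000 trials gives 18% without group and 5% with it.

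**4. Adding shared burn severity.** Let each outcome correlate λ with severity within arms. This adds λ² to the covariance. The values of λ are assumptions; the article gives none.

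| λ | Induced correlation, no group term | Significant, no group | Significant, with group | With group and severity |
|---|---|---|---|---|
| 0 | 0.15/1.150 = 0.13 | 18% | 5% | 5% |
| 0.3 | 0.24/1.150 = 0.21 | 40% | 11% | 5% |
| 0.5 | 0.40/1.150 = 0.35 | 83% | 53% | 5% |

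The last column assumes severity is fully captured. Depth and percent TBSA would do this only in part.

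**5. Overfitting.** The expected R² from p pure-noise predictors in a single-level regression is p/(n − 1). With 3 predictors, 66/3 = 22 children per predictor and R² = 3/65 = 0.05. With 20, 66/20 = 3.3 per predictor and R² = 20/65 = 0.31. Since p is not stated, no conclusion follows.

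**The case against.** The strongest defence is that this is a supplementary analysis described in one sentence of a condensed article. Entry method, predictor selection and covariates are normally left to the analysis plan, which is not shown. A coefficient on a later variable is simply an association. Demographic and clinical factors are named as predictors in the same sentence, so burn depth and percent TBSA may well be in the models. The earlier GEE does name treatment group.

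Much of this stands, and it rules out several stronger readings that a reader might infer:
- **Every outcome regressed on all the others in one overfitted model.** The text fits small or one-at-a-time models equally well.
- **An uncontrolled number of false positives.** The Šidák correction is planned where appropriate. It would limit chance findings, though not associations produced by treatment or severity.
- **The only route to the trial's headline claim.** The abstract's discussion says "Study results will elucidate whether the disease process can be changed by using medical hypnosis". That is a question of treatment effect, answered by the randomized comparison. The objectives contain no mechanism or mediation aim.
- **Reversed effects certain to be reported.** The sentence permits such tests; it does not ensure them.
- **The high rates at λ = 0.5 as an expected size.** They depend on an assumed loading and on severity being left out.

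What does not fall away is the stated rule. It fixes which variables may be predictors, calls their relation influence, and sets no time order. An analysis plan that followed it would carry the fault forward.

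**Conclusion.** The point holds in a limited form. As written, the sentence allows later outcomes to be tested as influences on earlier ones and does not name treatment group. On the planned effects and 66 children alone, omitting group would make healing a false influence on pain in about 18% of trials, against the nominal 5%. That figure assumes both planned effects are real, arms are equal, each child contributes one value per outcome, and the test is two-sided and unadjusted. Repeated values in a GEE would change the number but not the reason for it. Shared severity would raise the rate by an amount that depends on its strength and on whether it is adjusted for.

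This sentence does not affect the primary group comparison. Overfitting is not established.

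**What to change.** Reword the sentence in Data analysis so that:
- predictors are baseline factors, or outcomes measured before the dependent outcome, for example the value at the preceding dressing change;
- treatment group and burn severity (depth and percent TBSA) stay in every such model;
- days to re-epithelialization and three-month PTSD are not used as predictors of procedural outcomes;
- results are reported as exploratory associations, not as influence.

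The confounder list for pain in the same section should be brought into line, since it also names days to re-epithelialization.

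The cost is wording only: data are already collected at every dressing change, so the earlier values exist. The downside is fewer exploratory results. Children with a single dressing change would contribute nothing to models that use a preceding value.

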### Data storage

Data are protected in locked filing cabinets within the secure area of the Centre for Children’s Health Research, University of Queensland. Data are entered into a spreadsheet using Excel. Any incomplete data are coded as unknown, missing, or not applicable. The data set will be cleaned, checked, and then locked for analysis. Upon trial completion, data will be stored for 15 years as stipulated by the Queensland Children’s Health Services (LCCH) Human Research Ethics Committee.

### Dissemination

Outcomes will be published in a peer-reviewed medical journal (publication target *Burns*) and will also be reported at relevant conferences.

## Discussion

To our knowledge, this is the first RCT in the field of pediatric burn care investigating the impact of medical hypnosis on pain intensity, wound healing, procedural anxiety, biological stress markers, and PTSD development associated with wound care procedures. The neural mechanisms responsible for the antinociceptive effects of hypnosis have been rigorously studied by Rainville et al. [71, 72] and Faymonville et al. [73–78] by measuring regional cerebral blood flow (rCBF) using positron emission tomography. They independently reached the same conclusions: (1) Both the intensity (sensory component) and unpleasantness (affective component) of noxious stimuli are reduced during the hypnotic state, and (2) hypnotic pain modulation is chiefly facilitated by the anterior cingulate cortex [73]. Functional brain imaging studies like these not only help prove the existence of a hypnotic state but also validate the therapeutic effects of hypnotherapy in the medical setting [78].

As noted by early nineteenth-century physicians and surgeons going at least as far back as [name] (1795–1860), children and adolescents are especially “sensitive” to hypnotic techniques and responsive to hypnotherapeutic strategies for patient care [29]. In terms of clinical benefits, hypnotherapy can aid in decreasing at least two facets of the complex, multidimensional phenomenon of pain: the sensory component (tied to pain intensity) and the affective component (tied to the emotional experience of pain) [79]. In addition to hypnotic suggestions for analgesia and anxiolysis, the hypnotherapist is uniquely able to give posthypnotic suggestions prior to ending the pediatric patient’s trance.

Barber explains that posthypnotic suggestions are capable of causing dissociation of noxious perceptions, aiding in reducing the sensory and affective components of pain [80]. Successive hypnotherapy sessions have a cumulative effect, resulting in neuroplastic changes. Neural reorganization is thought to occur, such that pain responses are replaced by non-painful responses devoid of suffering that develop in response to originally noxious stimuli [80]. Barber also identifies the hypnotic effect as being enhanced by the clinical relationship and the establishment of good rapport [80].

Since one classic element of the therapeutic hypnotic state is a feeling of relaxation (i.e., increased parasympathetic tone), anxiety reduction goes hand in hand with clinical hypnosis. A randomized trial (*n* = 50, age 2–11 years) conducted by Calipel et al. compared the efficacy of hypnosis to reduce anxiety and perioperative behavioral disorders versus midazolam premedication in children [81]. The number of anxious children was significantly less during anesthetic induction in the hypnosis group (39 % versus 68 %, *p* < 0.05) [81]. Hypnosis reduced the frequency of postoperative behavioral disorders by about half on day 1 and day 7 relative to midazolam [81]. These findings suggest that hypnosis is more efficient at reducing preoperative anxiety in children compared to midazolam, with the added benefit of reducing behavioral disorders in the first two postoperative weeks.

Given the ease with which even preschool-aged children [48] use and learn simple self-hypnosis techniques for pain and anxiety management, and considering that a child’s successful use of self-hypnosis facilitates a sense of self-mastery and empowerment, this RCT seeks to validate medical hypnosis as a useful tool and opportunity to help manage or prevent the pain, distress, and negative psychological sequelae commonly associated with pediatric burns and wound care procedures.

